### **Cervical dilatation**

Will be examined immediately before randomization (after the woman has crossed the alert line of the partogram), when IMP is given (if there is more than 45 minutes between randomization and IMP). After IMP is given the midwife will examine the cervix according to ward routine, but at least every two hours.

**Questionnaire** Childbirth experience questionnaire (CEQ) developed and validated in Sweden consists of 22 items in 4 categories: own capacity, professional support, perceived safety and participation. We have added one question concerning request for caesarean section in next pregnancy

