## 9 STATISTICAL METHODS AND DATA ANALYSIS

### 9.1 Sample Size calculation

In this study, we will include 250 women.

The sample calculation was based on a randomized controlled trial by Dencker et al from 2009 (37) and a review by Neal et al (27). In the trial, Dencker et al randomized 630 Swedish women who developed slow progress in the first part of active labor. Their inclusion criteria, definitions and time of randomization are similar to what is planned for our study, but they measured the duration from randomization to delivery, in contrast to our scope, which is the duration from IMP is given to delivery. Still, descriptive statistics from their “Early oxytocin group” is important for our sample size calculations. Dencker et al. found that in this group, the mean duration from randomization to delivery was 5.2 hours, SD 2.8 hours. In the review by Neal et al., a total of 17 studies and 7009 nulliparous women were summarized to have a weighted mean duration of labor at 360 minutes (6 hours), and a standard deviation of 216 minutes (3.5 hours). The article states that the mean values “closely parallel those found at median.” Labor duration was calculated from onset of active phase, first stage, with a mean dilatation at start of active phase at 3.7 cm.

Our study will define active labor from 3 cm, and measure the duration from IMP is given to delivery. Since the intervention will not start until a woman crosses the alert line, the duration measured in the planned study, and the corresponding SD, will be expected to be shorter than the total duration and SD reported in Neal et al., which corresponds well to the numbers found in Dencker et al..

A mean difference of 60 minutes in labor duration is considered to be clinically relevant. Such a difference may be assumed to reduce the use of oxytocin, and it is realistic to obtain as all the other studies on spasmolytics found a difference of more than 55 minutes, with a mean difference all studies of 74 minutes.

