A methodological issue is that while both the articles we use as a basis for the sample calculations report means and SDs for the duration of labor, this outcome is a time-to-event outcome, with emergency cesarean delivery as a censoring event. The primary outcome will be treated as such in the analyses, and this should also be reflected in the power calculation. However, background data on our primary endpoint are hard to find, and we have therefore based our sample size calculation on the results from Dencker et al.

In the study population, the expected proportion of emergency cesarean delivery will be approximately 7%. Hence, most (approximately 93%) duration times will be observed, and a sample size based on a traditional continuous outcome e.g. a two-sample t-test will give a good indication for the sample size. Due to the inherent skewness of labor duration data, one can expect published values of SD to be slightly overestimated.

With the SD of 2.8 given in Dencker et al., and a power of 80 % we would need in total 246 women (123 women in each group) to discover a difference of 60 minutes. Furthermore, we calculate that

we will need written informed consent from at least 600 women to be able to randomize approximately 250 participants (8% [50 women] will be lost because of elective cesarean section, 25% [140 women] will be induced or receive oxytocin before 3 cm, and 40% [165 women] will not cross the alert line). In addition some of the eligible women will not be randomized because the midwife on duty forget to take the necessary steps and some participants will withdraw from the study.

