## **9.2 Randomization**

### **9.2.1 Allocation- sequence generation**

- The allocation sequence is based on computer-generated random numbers, and will be generated by an independent statistician
- the allocation ratio is 1 (equal probabilities to placebo and treatment)
- No stratification.

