### 9.5.1 Primary analysis

This protocol is designed to address a single primary endpoint, which is the duration of labor from when the participant was given IMP, to delivery

This is a time-to-event outcome, where vaginal delivery is the event of interest and emergency cesarean delivery is the censoring event.

The study is designed to establish the superiority of intravenously administered Butylscopolamine bromide compared to placebo on a single primary endpoint; the duration of labor from when the participant was given IMP, to delivery. The null hypothesis is that there is no difference in the duration of labor from when the participant was given IMP, to delivery, between the two treatment groups.

The alternative hypothesis is that there is a difference in the duration of labor from when the participant was given IMP, to delivery, between the two treatment groups.

Superiority of Butylscopolamine bromide on the duration of labor from when the participant was given IMP, to delivery, is claimed if the primary null hypothesis is rejected, and the group difference is in favor of Butylscopolamine bromide.

Statistical significance is claimed if the null hypothesis is rejected on the significance level (alpha) of 0.05 (two-sided). That is, if the p-value of the null hypothesis test is less than or equal to 0.05.

As there is only one identified primary analysis, there will be no adjustments for multiple testing in the secondary analyses. Secondary analyses on secondary endpoints will be regarded as supportive.

The primary endpoint will be analyzed using Weibull regression, and the p-value for the statistical hypothesis test for the primary endpoint will be the p-value from this analysis. Unadjusted Kaplan-Meier plots will be presented. The effect measures will include median (and quartiles) duration in the two treatment groups, and the proportion of women who give birth within 2, 4, 6, 8, 10 and 12

hours after randomization. All efficacy analyses will be presented by the size (point estimate) of the difference between the treatments and the associated 95% confidence interval.

The statistical analyses will be done in SPSS v23, or R version 3.5.0 (<https://www.r-project.org/>).

Robustness of the results will be checked using Cox regression, by including baseline characteristics known to be associated with labor duration as covariates, and performing the analyses with different options for data imputation.

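### The primary Weibull model is laid out as treatment-only, although cervical dilatation is measured just before randomization and could be a pre-specified covariate: lost efficiency, not an error

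*Protocol*

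**What the plan says.** Section 9.5.1 of the protocol names the confirmatory method: "The primary endpoint will be analyzed using Weibull regression". The same sentence makes the p-value from this analysis the primary one, judged at a "significance level (alpha) of 0.05 (two-sided"). No covariate is listed. The only mention of adjustment closes the section: "Robustness of the results will be checked using Cox regression, by including baseline characteristics known to be associated with labor duration as covariates".

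On dilatation itself, section 3.3 admits women from 3 cm to below 10 cm. Section 5.2 (Cervical dilatation) says that the cervix "Will be examined immediately before randomization (after the woman has crossed the alert line of the partogram"), so the value exists for every woman before allocation. Section 9.2.1 states "No stratification".

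Sections 9.4 and 9.5 leave full detail to a separate SAP, to be signed before database lock. That SAP is not at hand.

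**The concern.** The primary endpoint runs from the study injection to delivery. A woman randomized at 3 cm has further to go than one randomized at 8 or 9 cm, so part of the spread in the endpoint is probably already known at randomization. Neither the design nor, as laid out, the confirmatory test uses that information, and the robustness sentence does not name dilatation either.

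Three things are at stake: power at a fixed sample size; the effect of any chance imbalance in dilatation on the primary estimate; and a possible dispute afterwards if the treatment-only and adjusted results fall on opposite sides of 0.05 and only the former was designated as primary.

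**Working it through.** **Inputs from the protocol.** Section 9.1: target difference 1 hour ("A mean difference of 60 minutes in labor duration is considered to be clinically relevant"); for the source trial, "the mean duration from randomization to delivery was 5.2 hours, SD 2.8 hours"; sample size, "a power of 80 % we would need in total 246 women (123 women in each group"); planned enrolment 250, hence 125 per arm. Section 9.5.1: two-sided alpha 0.05. Section 1.3: mean dilatation rates of 1.2 and 1.4 cm per hour in two large studies of first-time mothers.

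**Step 1: reproduce the plan's figure.** n per arm = 2 × [SD × (1.960 + 0.842) / difference]² = 2 × (2.8 × 2.8016 / 1)² = 123.07. This agrees with 123 per group and uses the raw SD with no covariate. Power at 123 per arm is 0.800.

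**Step 2: adjust in the same terms.** If dilatation explains a share R² of the variance, the SD in the formula becomes 2.8 × √(1 − R²). With 125 per arm, SE = SD × √(2/125) and power ≈ Φ(1/SE − 1.96).

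| R² (assumed) | SD (h) | SE (h) | Power, normal | Power, t-test | n per arm for 80% (normal) |
|---|---|---|---|---|---|
| 0 | 2.800 | 0.354 | 0.806 | 0.803 | 124 |
| 0.1 | 2.656 | 0.336 | 0.845 | 0.842 | 111 |
| 0.2 | 2.504 | 0.317 | 0.884 | 0.882 | 99 |
| 0.3 | 2.343 | 0.296 | 0.921 | 0.919 | 87 |

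**Step 3: is an R² of that order plausible?** At 1.2 to 1.4 cm per hour, one centimetre takes 1/1.2 = 0.83 h to 1/1.4 = 0.71 h. Entry at 3 cm rather than 9 cm then means 6 × 0.71 = 4.3 h to 6 × 0.83 = 5.0 h more, against a 1-hour target. If dilatation at entry has an SD of 1 to 2 cm (assumed), R² = (slope × SD / 2.8)² runs from (0.71 × 1 / 2.8)² = 0.07 to (0.83 × 2 / 2.8)² = 0.35. This is an indication only: those rates come from first-time mothers in general, and the protocol gives no distribution of dilatation at entry.

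**Step 4: chance imbalance.** With an SD of 1 to 2 cm, the difference between arms in mean dilatation has SE = SD × √(2/125) = 0.13 to 0.25 cm. At an assumed 0.5 to 1 h per cm, the 95% range of the resulting shift is ±1.96 × 0.5 × 0.126 = ±0.12 h to ±1.96 × 1 × 0.253 = ±0.50 h, that is ±7 to ±30 minutes.

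**Step 5: Weibull check.** Simulation with 250 women, 1,000 runs per setting, shape about 1.94 (matching mean 5.2 h and SD 2.8 h), time ratio 4.2/5.2 = 0.81, and censoring at 7% (section 9.1) or 15% (the department's cesarean rate in alert-line women, section 1.5). R² here refers to log duration, with dilatation taken as uniform.

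| R² (assumed) | 7% censored: unadjusted / adjusted | 15% censored: unadjusted / adjusted |
|---|---|---|
| 0 | 0.90 / 0.90 | 0.86 / 0.85 |
| 0.1 | 0.86 / 0.92 | 0.85 / 0.92 |
| 0.2 | 0.81 / 0.93 | 0.83 / 0.94 |
| 0.3 | 0.82 / 0.97 | 0.77 / 0.96 |

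The simulation error is about one percentage point per entry. The direction agrees with Step 2; the levels depend on the assumed settings.

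**The case against.** The case for leaving the protocol alone has several parts.

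- **The model is not called unadjusted.** That word is attached only to the Kaplan-Meier plots, and the SAP may list covariates. This stands as a caution: the treatment-only reading is inferred. It is nevertheless the natural one, because covariates in the primary model would leave the robustness sentence little purpose. A SAP that moved them there would change what the protocol sets out.
- **Adjustment is already planned.** True, as a robustness analysis, so imbalance goes unaddressed only in the primary estimate and p-value. Randomization keeps that comparison unbiased, and its standard error already allows for chance imbalance.
- **No planned power is lost.** True. The sample size was computed without covariates and reproduces. A reader might infer that the trial is underpowered. The documents do not support that. Simulated unadjusted power of 74% to 79% can be obtained with a time ratio of 0.83, but the protocol's own figures give 0.81. The entry of 0.77 in Step 5 needs R² of 0.3 and 15% censoring together.
- **The strength of the predictor is not sourced.** True. Calling dilatation the strongest known predictor would go beyond the documents. The endpoint includes the second stage, and 72% of alert-line women receive oxytocin (section 1.5); both could weaken the link.
- **The hazard ratio is not a named effect measure.** Omitting a prognostic covariate pulls a hazard ratio toward 1, but section 9.5.1 reports medians, quartiles and proportions delivered, so that argument carries little weight here.

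A reader might also infer an inflated false-positive rate. In one simulated null setting (R² 0.3, 7% censored, 3,000 runs) rejection was 7.2% unadjusted and 5.3% adjusted, because the pooled times are then no longer Weibull. That rests on assumed inputs and does not establish a defect in this trial.

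**Conclusion.** The point holds as one of efficiency. By its layout the protocol fixes a treatment-only confirmatory model and leaves unused a baseline value that is collected for every woman and plausibly related to the endpoint. On the protocol's own approximation, adjustment is worth about 4, 8 or 12 percentage points of power at R² of 0.1, 0.2 or 0.3, and nothing at R² of 0. The R² values are assumptions that the documents neither give nor rule out. The planned test remains unbiased and meets its stated 80%, so the change is advisable rather than necessary for validity.

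**What to change.** In section 9.5.1 and the SAP, before database lock and unblinding, state that the primary Weibull regression contains treatment and cervical dilatation as measured immediately before randomization, and that the primary p-value comes from this model. Fix the form of the dilatation term in the SAP.

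Use the pre-randomization value, not the re-check made when the study injection is given more than 45 minutes after randomization. The re-check is required only for delayed women and follows allocation, so mixing the two would give the covariate different meanings for different women.

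Report the treatment-only Weibull model as supportive. Keep the medians, quartiles, proportions delivered by fixed times and Kaplan-Meier plots as unadjusted summaries, so that it is clear which figures are adjusted.

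The cost is about one sentence in each document. No new data, visits or participants are needed, and section 9.4 allows amendments to the analysis plan until database lock.

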### **9.5.2 Secondary analyses**

Secondary endpoints in this study contain

1. Time-to-event variables (duration of labor from the time when the participant was given IMP to 10 cm dilatation, and duration of labor from the onset of active labor (at least 3 cm dilatation) to delivery,
2. Continuous variables (mean cervical dilatation, amount of oxytocin given, pain scores on VAS scales, pH values from umbilical artery and vein, postpartum hemorrhage and responses to CEQ),
3. Categorical or discrete variables (mode of delivery, admission to Neonatal Intensive Care Unit, urinary retention, anal sphincter injuries and Apgar scores).

Time-to-event variables will be analyzed as the primary endpoint.

Continuous and categorical variables will be analyzed by simple bivariate analyses (t-test, Mann-Whitney test or Pearson chi square test, as appropriate), with linear or logistic regression as robustness analyses.

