#### **Amount of oxytocin given, measured**

1. As total time with treatment (continuous variable)
2. As International Units (IU). The midwife measures mL of oxytocin solution given

during labor. IU are calculated based on standardized concentration of the infusion solution [10 IU oxytocin in 1000 mL NaCl solution] (continuous variable).

Pain scores using a Visual Analogue Scale at baseline and 30 minutes after administration of each dose of IMP (continuous variable)

Postpartum hemorrhage (continuous variable)

Urinary retention, defined as need for urinary catheter before the participants leave the delivery ward (categorical variable)

Anal sphincter injury (categorical variable)

*Endpoints regarding the infant:*

Apgar score at 5 minutes and 10 minutes after delivery (ordinal variables)

pH levels in umbilical vein and artery after delivery (continuous variables)

Admission to the Neonatal Intensive Care Unit (categorical variable)

*Postpartum endpoints:*

Birth experience measured by the validated questionnaire Child Birth Experience Questionnaire (continuous variables for each sub category)

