| b Vital signs mother                          |                  | X                                                                              | X            |                           | X                          | X                               |                      |
| Cervical dilatation                                      |                  | X                                                                              |              |                           |                            |                                 |                      |
| Pain measurement (VAS)                                   |                  |                                                                                | X            | X                         |                            |                                 |                      |
| Treatment administration                                 |                  |                                                                                | X            |                           |                            |                                 |                      |
| Adverse event, mother                                    |                  |                                                                                | X            | X                         | X                          | X                               |                      |
| Adverse event, newborn/fetus                             |                  |                                                                                | X            | X                         | X                          | X                               |                      |
| c Physical Examination newborn (pediatrician) |                  |                                                                                |              |                           |                            | 1 st day post partum |                      |
| Questionnaire (Delivery experience)                      |                  |                                                                                |              |                           |                            |                                 | X                    |

aPhysical Examination fetus (CTG) includes continuous fetal heart rate tracing.

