#### **5.2.1 Before Treatment Starts**

- Eligibility will be assessed by the inclusion chart
- Baseline is defined as the time point in labor when slow progress is detected. At baseline, vital signs from mother and fetus will be obtained, and we will perform baseline observations regarding medical history
- For the endpoint pain baseline measurements by a VAS scale will be obtained before randomization

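### VAS pain is to be compared mainly by an unadjusted bivariate test although a pre-treatment score is collected from every woman, and the protocol gives two times for that score

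*Protocol*

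**What the plan says.** **Analysis.** Section 9.5.2 lists VAS pain among the continuous secondary endpoints and states: "Continuous and categorical variables will be analyzed by simple bivariate analyses (t-test, Mann-Whitney test or Pearson chi square test, as appropriate". The same sentence then gives linear or logistic regression as robustness analyses and names no covariate. Section 9.5.1 calls the secondary analyses supportive, and promises a point estimate of the treatment difference with a 95% confidence interval for all efficacy analyses.

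**Measurement.** Section 5.2 (under Informed consent) asks all women to rate pain before treatment starts and 30 minutes after. Section 5.2.2 says efficacy on pain is assessed by the 30-minute VAS. No section says whether the level or the change from baseline is compared.

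**Timing of the first score.** Section 5.2.1: "For the endpoint pain baseline measurements by a VAS scale will be obtained before randomization". In the flow chart (section 5.1, Table 1) the row "Pain measurement (VAS" is empty under the baseline column, which is the crossing of the alert line. It is marked at IMP administration and at 30 minutes after.

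**Endpoint wording.** The list in section 1.7 reads: "Pain scores using a Visual Analogue Scale at baseline and 30 minutes after administration of each dose of IMP". The synopsis and section 6.1 give the same endpoint without reference to each dose, and the synopsis, section 2 and section 4.3 state a single dose.

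**The concern.** A pre-treatment measurement of the outcome is usually the strongest covariate available, and here it costs nothing further to collect. Section 9.5.2 gives it no role in the main test, except possibly through a change score. Section 9.2.1 specifies no stratification, so a chance difference between the arms in baseline pain would stay in the headline result if the 30-minute level is compared. A change score would over-correct for it whenever the correlation is below 1 (equal SDs). At stake are the width of the confidence interval for pain and the power to see an effect on it. No power calculation is given for pain.

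The two times for the baseline score matter because section 4.2 provides for IMP being given more than 45 minutes after randomization, a gap long enough to require a new cervical examination. If staff follow different parts of the protocol, the baseline will be taken at different points of labor in different women. No later analysis plan can repair that.

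**Working it through.** **1. The plan's own calculation.** Section 9.1 sizes the trial on the primary endpoint only: "the mean duration from randomization to delivery was 5.2 hours, SD 2.8 hours", and "a power of 80 % we would need in total 246 women (123 women in each group) to discover a difference of 60 minutes". Section 9.5.1 gives "the significance level (alpha) of 0.05 (two-sided", and section 9.2.1 gives "the allocation ratio is 1 (equal probabilities to placebo and treatment". Then

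n per arm = 2 × [2.8 × (1.960 + 0.842) / 1]² = 123.07.

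This rounds up to 124 per arm (248 in total). The plan's 123 per arm gives a power of 0.7998. The figure reproduces, but it has no bearing on pain: the documents give no SD, effect size, power or correlation for VAS.

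**2. Variances for pain.** Let r be the correlation between baseline and 30-minute VAS. It is an assumption, shown over a range. Assume equal SDs at both times, and set the variance of the 30-minute level to 1. The variance that enters the treatment comparison is then:

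- 30-minute level: 1
- change score: 2(1 − r)
- ANCOVA: 1 − r² (ignoring the one degree of freedom for the slope, negligible with 250 women)

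The ratios to ANCOVA are 1/(1 − r²) for the level and 2(1 − r)/(1 − r²) = 2/(1 + r) for the change.

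| r (assumed) | ANCOVA variance | Change variance | Level ÷ ANCOVA | Change ÷ ANCOVA |
|---|---|---|---|---|
| 0.1 | 0.99 | 1.80 | 1.01 | 1.82 |
| 0.3 | 0.91 | 1.40 | 1.10 | 1.54 |
| 0.5 | 0.75 | 1.00 | 1.33 | 1.33 |
| 0.7 | 0.51 | 0.60 | 1.96 | 1.18 |

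**3. Reading the table.** The two ratios are equal when 1 = 2(1 − r), that is at r = 0.5. Below 0.5 the level is the better unadjusted choice; above 0.5 the change is. So even if the better of the two were picked with r known, its variance could be up to 1.33 times that of ANCOVA, and no more. The larger ratios arise only when the less suitable one is used.

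**4. Detectable difference.** With 125 per arm, two-sided 0.05 and 80% power, in units of the 30-minute SD:

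- level: 2.802 × √(2/125) = 0.354 at any r
- ANCOVA: 0.354 × √(1 − r²) = 0.338, 0.307 and 0.253 at r = 0.3, 0.5 and 0.7
- change: 0.354 × √(2(1 − r)) = 0.419, 0.354 and 0.274 at the same values

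These formulas describe comparisons of means. They do not carry over exactly to the Mann-Whitney test.

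**5. Timing, side by side.** Section 5.2.1 says before randomization. The flow chart says at IMP administration. Section 5.2 (under Informed consent and under Pain measurement) says only before treatment or administration. All can be read as pre-treatment, but the first two are different moments, and section 4.2 allows more than 45 minutes between them.

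**The case against.** The strongest reply is that this belongs to the statistical analysis plan. Section 9.5.2 gives a generic sentence qualified by a proviso of appropriateness, and sections 9.4 and 9.5 defer full detail to a separate SAP, which is not at hand. The planned robustness regression could carry the baseline VAS. A t-test or Mann-Whitney test is valid under 1:1 randomization, and pain is only a supportive endpoint.

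Most of that stands. It cannot be said that the baseline score goes unused in the trial. But the protocol does more than leave detail open: it ranks the bivariate test first and regression as robustness. An SAP that made ANCOVA the main pain analysis would depart from that wording.

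A reader might infer stronger things that the documents do not support:

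- **That the planned test is biased or invalid.** It is neither; the loss is of precision.
- **That the trial forgoes the equivalent of 96% more women.** That figure needs r = 0.7 and a comparison of the level alone. Against a change score the gain at r = 0.7 is 18%, and against the level at r = 0.1 it is about 1%. Section 5.2.2 points towards the level, but no section settles it.
- **That r must be high because labor pain varies widely and rises with dilatation.** The protocol does not say this. Section 4 allows oxytocin at the same time as the study drug, so a high correlation cannot be presumed.
- **That the flow chart makes the baseline a post-treatment score.** Section 5.2 places it before treatment, so either time would be a legitimate covariate in a blinded trial. The fault is that there are two.

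**Conclusion.** The point holds as one of efficiency and consistency. The main pain analysis is fixed as an unadjusted test although a baseline score is planned for every woman. ANCOVA is at least as precise as either reading of that test. For r between 0.1 and 0.7 the unadjusted variance is 1.01 to 1.96 times that of ANCOVA if the level is compared, and 1.82 to 1.18 times if the change is compared. These figures rest on an assumed correlation and equal SDs. They concern a supportive secondary endpoint and leave the primary analysis and its conclusion untouched.

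The conflict over the time of the baseline VAS, and that between the reference to each dose in section 1.7 and the single dose elsewhere, need no assumption: both can be read directly from the protocol.

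**What to change.** 1. In section 9.5.2 (and the SAP), make the main analysis of VAS pain a linear regression of the 30-minute score on treatment and baseline VAS. Report the adjusted mean difference with its 95% CI, and keep the bivariate test as robustness.
2. Reconcile section 5.2.1 and the flow chart so that both give the same single pre-treatment time for the baseline VAS.
3. Reconcile the reference to each dose in the section 1.7 pain endpoint with the single dose stated in the synopsis, section 2 and section 4.3.

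The cost is one analysis sentence, one flow-chart entry and one endpoint line. No extra women or measurements are needed. Section 9.4 allows the analysis plan to be amended until database lock, so the first change can be made before unblinding. The second helps only women not yet measured; for those already enrolled, the recorded time of the baseline VAS, where available, should be reported.
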